## Abstract

**Background:**

Previous studies have indicated that acupuncture can alleviate the symptoms of Tourette syndrome (TS), but the evidence is insufficient. So far, there have been no reports on plum-blossom needle therapy for TS. Here we present a protocol for a randomized controlled trial using plum-blossom needle therapy to treat TS.

**Methods/design:**

Sixty patients will be randomly allocated into either the plum-blossom needle therapy group or the habit reversal training (HRT) group. All patients in each group will be given 12 weeks of treatment, with follow-up at the 24th week. The primary outcome measure will be the mean change from baseline in the total tic score on the Yale Global Tic Severity Scale (YGTSS) at the 12th week. Secondary outcome measures will include the scores on the TS Clinical Global Impression Scale (CGI) and the mean changes from baseline in the YGTSS score and the Children and Adolescents’ Quality of Life Scale (CAQOL) at other time points. Safety will also be evaluated.

**Discussion:**

This trial will evaluate the effectiveness and safety of plum-blossom needle therapy for TS compared with HRT. A limitation of this trial is that patients and acupuncturists cannot be blinded.

**Trial registration:**

ClinicalTrials.gov Identifier: NCT02403258 (Date of registration: March 31, 2015).

## Background

Tourette syndrome (TS) is a childhood-onset chronic neuropsychiatric disorder characterized by multiple motor tics and one or more vocal tics, with a duration of at least 1 year [1]. Population-based studies indicate that TS affects approximately 0.3–1 % of children in Western countries [2–6] and 0.43–0.56 % of children in China [7, 8]. TS is two to four times more common in boys than girls [5]. The majority of TS cases have comorbid conditions such as attention-deficit hyperactivity disorder, obsessive-compulsive disorder, mood disorders, learning disorders, self-injurious behavior, and other behavior disorders. TS and its complications seriously influence the quality of patients’ lives [9, 10].

The guidelines developed by the European Society for the Study of Tourette syndrome (ESSTS) in 2011 recommended that TS could be treated by behavioral therapy (habit reversal training or exposure with response prevention) and medications including alpha-adrenergic agents, typical antipsychotics, atypical antipsychotics, and benzamides [11, 12]. Although there is strong evidence in favor of pharmacological intervention, it is also known that medications can rarely eradicate tics completely and are always associated with unwanted side effects. The most commonly observed adverse events of typical antipsychotics are extrapyramidal reactions, neuroleptic malignant syndrome, drowsiness, restlessness, and sexual dysfunction; sulpiride may lead to sustained sedation or drowsiness [13–15].

Acupuncture is a conventional Traditional Chinese Medicine method that dates back thousands of years, and it has specifically been used to treat TS for many years. A Chinese systematic review of six randomized controlled trials published in 2010 revealed that acupuncture was probably more effective for TS than medications [16]. However, the included studies were all published in Chinese, with the limitations of small sample sizes and poor design quality; the systematic review could not provide sufficient evidence to support the effectiveness of acupuncture in treating TS.

At present, many parents in China seek treatment from Traditional Chinese Medicine practitioners for their children with TS. However, maintaining a fixed position during conventional acupuncture is difficult for children, and the pain associated with conventional acupuncture leads to poor compliance. Plum-blossom needle therapy is a method of shallow insertion of multiple needles into the skin. The treatment instrument is made of five or seven stainless-steel needles arranged in a plum-blossom-shaped pattern, hence the name ‘plum-blossom needle.’ Plum-blossom needle therapy treats diseases by tapping specific skin areas or acupoints corresponding to the treatment of different illnesses based on the meridian theory. Our pilot study in which we used self-made blunt-pointed plum-blossom needles showed that plum-blossom needle therapy can relieve the symptoms of TS. The treatment was well accepted by children with TS because of its mild pain as the needles did not pierce the skin.

This protocol is designed for phase II of our trial. The objective of this trial is to evaluate the effectiveness and safety of plum-blossom needle therapy for treating TS.

## Methods/design

### Study design

This protocol is for a prospective randomized controlled trial. Randomization will be performed by the Good Clinical Practice (GCP) office of Guang’anmen Hospital of the China Academy of Chinese Medical Sciences. Statistics Analysis System software version 9.1.3 (SAS Institute, Cary, NC, USA) will be used to generate the random allocation sequence with a block of four. Opaque sealed envelopes will be used. Patients' sequence numbers are printed on the envelope surface. The random allocation sequence numbers and group names are inside the envelope. The randomization program will be saved by an appointed staff member in the GCP office who will not take part in this trial.

The trial will be conducted in Guang’anmen Hospital over 3 years from 1 January 2015 to 30 May 2018. We plan to recruit participants via advertisements in newspapers, television, websites, and posters. Eligible participants diagnosed with TS by a psychiatrist will be randomly assigned into the plum-blossom needle therapy group or the HRT group at a 1:1 ratio. A flowchart of the trial procedure is presented in Fig. 1.

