## Discussion

Traditional plum-blossom needles pierce the skin when treating disease. However, to improve patient compliance in this proposed trial, we will use self-made blunt-pointed plum-blossom needles that will not pierce the skin and hence will alleviate the pain during treatment.

The primary aim of this study is to evaluate the effectiveness of plum-blossom needle therapy for TS. As the blunt-pointed plum-blossom needles will not pierce the skin, we cannot feasibly conduct sham plum-blossom needle therapy or placebo as a control group. HRT, recommended as an effective and safe TS treatment by the ESSTS, is the most extensively researched behavioral treatment for tics. Hence, comparing plum-blossom needle therapy with HRT will reflect the effectiveness and clinical value of plum-blossom needle therapy for TS. Most studies of HRT for TS have 10–14-week-long treatment, with follow-up data at 1 month to 1 year, mostly 3 months post-treatment. Thus, it is appropriate to conduct the follow-up visit at the 24th week after the last-time treatment [12, 19–21]. We will therefore measure the primary outcome at the 12th week, but we will also observe the changes in outcome measurements at the 4th, 8th, and 24th week to observe the time of onset and maintenance of the effect produced by plum-blossom needle therapy. In this trial, patients and acupuncturists will not be blinded, which means bias cannot be avoided. However, we can partially avoid biases caused by expectations and subjective assessment via rigid randomization, concealment of the allocation, and blinding of outcome assessors and statisticians. Otherwise, the outcome of this trial could not exclude the possible placebo effect of plum-blossom needle therapy, so we would not know its true efficacy.

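### A single published block size of four in an open-label, one-hospital trial weakens allocation concealment: staff who know the earlier allocations could deduce about one third of assignments

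*Protocol article*

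**What the plan says.** Under Study design, the protocol article says that SAS "will be used to generate the random allocation sequence with a block of four". Eligible participants "will be randomly assigned into the plum-blossom needle therapy group or the HRT group at a 1:1 ratio". The Abstract gives the total: "Sixty patients will be randomly allocated into either the plum-blossom needle therapy group or the habit reversal training (HRT) group". The setting is one hospital: "The trial will be conducted in Guang’anmen Hospital over 3 years from 1 January 2015 to 30 May 2018". No stratification and no variation in block size is mentioned.

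Concealment rests on envelopes ("Opaque sealed envelopes will be used"), and the patients' "sequence numbers are printed on the envelope surface". Randomization is the task of the hospital's GCP office, and the program is kept there by someone outside the trial.

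The Discussion accepts the lack of blinding: "In this trial, patients and acupuncturists will not be blinded, which means bias cannot be avoided". It then lists what is meant to offset this in part: "rigid randomization, concealment of the allocation, and blinding of outcome assessors and statisticians". Trial status reports two participants recruited at the time of writing.

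**The concern.** Opaque envelopes stop someone reading the next assignment, and off-trial custody stops someone seeing the list. Neither stops someone working out the next assignment from past allocations and a known block size. With 1:1 blocks of four, the last patient of each block always goes to the arm with a place left. The third is equally determined whenever the first two match.

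Past allocations are not hard to observe here. One arm attends twice a week for needle tapping by an acupuncturist. The other attends weekly for training with a rehabilitation therapist in the same hospital. Sixty patients over about three years is fewer than two a month (60/36 = 1.7), so keeping a tally takes little effort.

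What is at stake is selection at entry. Someone who knows the next arm can decide whom to approach, or when, according to severity or expected cooperation. Blinded outcome assessment does not correct this, because it acts after the groups have been formed.

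**Working it through.** **The plan's own figure.** The article gives no figure for predictability. The only planned number used here is the total of 60, and it can be reproduced from Sample size and statistical analysis:
- Difference: 13.12 − 9.50 = 3.62.
- Common SD: √((5.40² + 3.20²)/2) = 4.44.
- One-sided α = 0.025, power 80%, normal approximation: n = 2 × (1.960 + 0.842)² × 4.44² / 3.62² ≈ 23.6, so 24 per group.
- Dropout of 20%: 24/0.8 = 30 per group, 60 in total, as stated.

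**Inputs.** Block size 4, ratio 1:1, one hospital (Study design); 60 patients (Abstract); 2 already recruited (Trial status). Assumptions: one unstratified list, and an observer who knows all earlier allocations.

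**Certain allocations.** There are C(4,2) = 6 equally likely blocks: AABB, ABAB, ABBA and their mirror images.

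| Position in block | P(assignment is certain) | P(best guess is right) |
|---|---|---|
| 1 | 0 | 1/2 |
| 2 | 0 | 2/3 |
| 3 | 1/3 (first two match: AABB, BBAA) | 1/3 × 1 + 2/3 × 1/2 = 2/3 |
| 4 | 1 | 1 |
| Mean over the block | (1/3 + 1)/4 = 33.3% | (1/2 + 2/3 + 2/3 + 1)/4 = 70.8% |

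**Over the trial.** 60/4 = 15 complete blocks, each with one certain allocation plus a second with probability 1/3.
- Expected number certain: 15 × 4/3 = 20.
- SD: √(15 × 1/3 × 2/3) = 1.8.
- Possible range: 15 to 30.
- The first two patients of a block are never certain, so with two recruited all of the expected 20 were still to come among the remaining 58.

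**Alternatives.** The fixed sizes were enumerated. The mixed sizes were simulated over 60-patient sequences (1,500 runs each), with an observer who knows the set of sizes and all past allocations, but not which size is in use. The sets are illustrative.

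| Scheme | Certain | Best guess right |
|---|---|---|
| Fixed 4 (as planned) | 33.3% | 70.8% |
| Fixed 6 | 25.0% | 68.3% |
| Fixed 8 | 20.0% | 66.6% |
| Random 4/6 | 5.5% | 69.1% |
| Random 2/4/6 | 4.1% | 70.0% |
| Random 4/6/8 | 2.3% | 67.8% |

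A larger fixed block still leaves a fifth to a quarter of assignments certain. Random variation removes most of the certainty, but it lowers the best-guess rate by only 1 to 3 percentage points.

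**The case against.** The strongest objection is that the arithmetic needs a condition the article does not establish: that the people enrolling patients know the earlier allocations. A psychiatrist diagnoses, acupuncturists treat one arm, a rehabilitation therapist treats the other, and blinded research assistants assess. The article does not say which of them enrols or opens envelopes. This stands. The one-third figure describes what an informed observer could deduce, not what any recruiter is shown to know. The text does not prevent such knowledge either, and the blinded roles it names are outcome assessors and statisticians, not recruiters.

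A reader might also infer that the envelopes lie in the recruiting clinic. No section says so. The GCP office performs the randomization, and it may already release allocations one by one. Consent before randomization and eligibility before assignment are stated too, so those steps are not missing. Only the order of the baseline YGTSS and the opening of the envelope is left open.

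A reader might further conclude that any resulting bias is beyond repair. That is too strong for severity. The baseline YGTSS is collected, so an imbalance would be visible and could be partly adjusted for. It does hold for unmeasured traits, such as expected cooperation, which plausibly matters for habit reversal training.

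Finally, varying the block size barely changes best guessing. That is correct. The case for the change rests on removing certainty, the most easily exploited form of foreknowledge.

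**Conclusion.** The point holds as a weakness in a stated design choice. A single block size of four, disclosed with 58 of 60 patients still to be enrolled in an open-label trial at one hospital, weakens the concealment that the Discussion counts among its safeguards. To staff who know the earlier allocations, on average one third of assignments (about 20 of 60, at least 15) are certain, and best guessing is right 71% of the time instead of 50%.

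This rests on two assumptions: one unstratified list, inferred because the article states no strata, and enrolling staff who know past allocations, which is feasible but not shown. The arithmetic itself is exact.

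It would go too far to say that concealment is defeated. Two thirds of assignments stay uncertain even to a fully informed observer, and the Discussion presents concealment as one of several measures that avoid bias only in part. Nothing in the article shows that selection has taken place, and the document does not contradict itself here. The change is worth making because it costs almost nothing, whereas steering on unmeasured traits could not be undone later.

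**What to change.** 1. Have the GCP office regenerate the unused part of the list with randomly varying block sizes, for example 4, 6 and 8. Keep the sizes from recruiting and treating staff, and out of anything published, until recruitment closes. Certain knowledge falls from 33% to about 2%. Best guessing falls only from 71% to about 68%, so secrecy of the scheme matters as much as the variation.
2. State that each allocation is opened only after the baseline YGTSS has been recorded, in addition to the eligibility and consent steps already described.
3. State who enrols patients, who holds and opens the envelopes, and whether those people can see earlier allocations. If the GCP office already releases allocations singly, one sentence settles this.

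The cost is minor programming in the office that already holds the list, and a possible small final imbalance. In the worst case, a block of four abandoned after two like assignments leaves a difference of 2, and a last block of eight cut after four like assignments adds 4. That gives 33 against 27. The variance of the mean difference, with equal SDs, would then rise by a factor of (1/33 + 1/27)/(2/30) = 1.01, or about 1%.

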**Fig. 1 Fig1:**
[figure not shown]
Flowchart of the proposed trial procedure

The duration of the study will be 25 weeks, including a baseline period of 1 week (week 0–1), a treatment period of 12 weeks (week 1–12), and a follow-up period of 12 weeks (week 13–24). The timeline of the trial is presented in Fig. 2.

**Fig. 2 Fig2:**

Proposed timeline of the trial

### Ethical approval

All procedures will be explained to patients and their guardians; the informed consent form will be reviewed and signed by each participant and their guardian before randomization. The trial protocol is in accordance with the principles of the Declaration of Helsinki (version Edinburgh 2000) and has been approved by the Ethics Committee of Guang’anmen Hospital, China Academy of Chinese Medical Sciences (ethics approval no. 2014EC104).

### Participants

A target sample of s60 participants with TS will be recruited in the trial.

#### Inclusion criteria

Participants must meet the diagnostic criteria of the Diagnostic and Statistical Manual of Mental Disorders of the American Psychiatric Association (DSM-IV-TR) for TS: Both multiple motor and one or more vocal tics have been present at some time during the illness, although not necessarily concurrently. The tics occur many times (usually in bouts) nearly every day or intermittently throughout a period of more than 1 year; during this period there was never a tic-free period of more than 3 consecutive months. Onset was before the age of 18 years. The disturbance is not due to the direct physiological effects of a substance (e.g., stimulants) or a general medical condition (e.g., Huntington’s chorea or postviral encephalitis) [1].Age 7 to 18 years.Participants must agree to participate in the trial, and both guardians and subjects must sign written informed consent.

#### Exclusion criteria

TS patients with concurrent severe problems involving the heart, liver, or kidney, or with hyperthyroidism.After evaluation by psychiatrists based on the Kiddie-Sads-Present and Lifetime Version, those who have comorbid conditions such as mental retardation, pervasive developmental disorder, schizophrenia, manic episode, bipolar disorder, anxiety and depression, or a specific learning disorder will be excluded.Tic symptoms caused by drugs.Subjects who are using pharmacological or non-pharmacological treatment for TS have to be free from that for at least 2 weeks prior to baseline assessment.Patients with a history of psychotropic substance or alcohol use during the 3 months preceding screening.Patients with a history of non-responsiveness to HRT and those participating in another clinical trial.

### Intervention

Lifestyle education will be taught to all parents/guardians of patients, including the stability and unity of the family, not being strict with their children, and reducing patients’ psychological burden. Patients will also be required to abstain from exciting novels and films. All participants must not receive any other therapy for TS during the trial.

### Plum-blossom needle therapy group

The acupoints were selected based on our pilot study and consensus with experienced acupuncture experts. The points will be DU20 (Baihui), DU16 (Fengfu), GB20 (Fengchi), EX-HN5 (Taiyang), BL15 (Xinshu), BL18 (Ganshu), and BL23 (Shenshu). Self-made head-detachable sterile plum-blossom needles will be used in this trial (see Fig. 3). After the skin has been wiped with 75 % alcohol, plum-blossom needles will be tapped perpendicularly on the skin at the selected acupoints with wrist force and then lifted immediately (see Fig. 4). Each point will be tapped repeatedly for 30 s and totally 6 min for each session. Acupuncturists should tap the points gently to make patients feel only a little pain and stop when the skin gets flushed but is not bleeding. The treatment will be two sessions per week for 12 weeks (24 sessions in all). Treatments will be done by acupuncturists with over 2 years of working experience and academic credentials above an undergraduate degree; they will be trained specifically for this protocol prior to the trial.

**Fig. 3 Fig3:**
[figure not shown]
Composition of the plum-blossom needle with a detachable head. Each needle head will be used for a specific patient and will be sterilized at high pressure after each use

**Fig. 4 Fig4:**
[figure not shown]
Manipulation of the plum-blossom needle

### HRT group

HRT will consist of the following: (1) self-monitoring, (2) competing responses, (3) relaxation training, and (4) contingency management. Self-monitoring will be done to increase patients’ awareness of premonitory sensations or urges and to obtain detailed descriptions of varied tic symptoms. Patients will be provided with charts in which they can record the occurrence of tics, preceding sensations/urges, and the muscles and movements involved in a tic. Competing response training will involve each patient being trained to perform more appropriate physical responses when they feel the urge to perform tics, thereby preventing tic occurrence. For example, patients with arm jerking tics will be trained to contract the tic-opposing muscles when they are aware of the early sensations or urges preceding tics. For vocal tics, competing responses such as closing the mouth and breathing slowly through the nose will be used to avoid occurrence of tics. For complex tics, competing responses for individual components will be developed first and then chained. Patients will also be taught the relaxation techniques of thoracic breathing and diaphragmatic breathing. Treatment will typically be started with the patients’ most bothersome tics, unless the patient and clinician determine that competing responses for a less bothersome tic would be easier to implement before moving on to a more bothersome/severe/complex tic [17, 18]. The HRT training will be given weekly for 12 weeks (12 sessions in total) by a special rehabilitation therapist. The first two sessions will be 1.5 h, and the remaining sessions will be 1 h for each treatment.

### Outcome measures

The primary outcome measure will be the mean change from baseline in the total tic score on the Yale Global Tic Severity Scale (YGTSS) at the 12th week.

Secondary outcome measures will include the mean change from baseline in the YGTSS score at the 4th, 8th, and 24th week, the mean score on the TS Clinical Global Impression Scale (CGI) at the 4th, 8th, 12th, and 24th week, and the mean score change compared with baseline on the Children and Adolescents’ Quality of Life Scale (CAQOL) at the 12th and 24th week.

Adverse events including fainting, stabbing pain during acupuncture, fatigue, insomnia, appetite change, worsening of symptoms, local infections, and other side effects related to acupuncture will be recorded in detail by patients, their parent/guardian, acupuncturists, and interviewers.

The outcome assessments will be done by research assistants who are blinded to the clinical management.

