## Trial status

The first participant was included on 3 January 2015. To date, two participants have been recruited.

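### The four CGI comparisons ignore the baseline severity that the trial already collects: valid, but less precise than they could be at no cost

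*Protocol article*

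**What the plan says.** The Outcome measures section of the protocol article treats its secondary scales in two ways. YGTSS is assessed as "the mean change from baseline in the YGTSS score at the 4th, 8th, and 24th week" and quality of life as "the mean score change compared with baseline on the Children and Adolescents’ Quality of Life Scale (CAQOL) at the 12th and 24th week". The CGI is "the mean score on the TS Clinical Global Impression Scale (CGI) at the 4th, 8th, 12th, and 24th week", a score and not a change. The abstract draws the same distinction, so it is not a slip of wording.

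The Sample size and statistical analysis section gives one rule for continuous data, a t-test or a nonparametric test, two-sided at 0.05. It names no covariate.

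The article does not say whether the CGI rates current severity or improvement since the start. The study design section provides a one-week baseline period but does not list what is assessed in it, and refers elsewhere for the schedule: "The timeline of the trial is presented in Fig. 2". The content of that figure is not available to this review.

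**The concern.** As the method stands, the CGI is the only efficacy scale whose comparison takes no account of where each child began. YGTSS and CAQOL do so through the change score. If starting severity predicts the later CGI, part of the spread in CGI scores within each arm is explainable, and a plain two-sample test leaves it in the error term.

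What is at stake is the width of four confidence intervals and the power of four secondary tests in a trial of 60 children. The primary outcome and the sample size are not affected. The information needed is already in the data, because a baseline YGTSS is required to compute the primary outcome.

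**Working it through.** **The plan's own figure.** The article states no power for the CGI. Its only calculation is for the YGTSS, from the pilot reductions of 13.12 ± 5.40 and 9.50 ± 3.20.

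- Difference: 13.12 − 9.50 = 3.62.
- Pooled SD: √((5.40² + 3.20²)/2) = √19.70 = 4.44.
- n per arm: 2 × (4.438 × (1.960 + 0.842)/3.62)² = 23.6, rounded up to 24.
- With 20% dropout: 24/0.8 = 30 per arm, as stated.

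The CGI does not enter this, so nothing below changes the sample size.

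**Inputs for the CGI.** n = 30 per arm and two-sided α = 0.05 come from the article. The correlation r between baseline covariate and follow-up CGI is not given; 0.3 to 0.6 is assumed. A true difference of 0.5 SD is also assumed, for illustration.

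**Is the raw comparison valid?** In 20,000 simulated randomised trials with no treatment effect, 30 per arm and r = 0.7, the unadjusted t-test on follow-up scores rejected in 5.0% of trials. Validity is not in question.

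**Precision.** In SD units, the standard error of the arm difference is:

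- raw score: √(2/n) = √(2/30) = 0.258
- change score: √(2(1 − r) × 2/n)
- baseline-adjusted score: √((1 − r²) × 2/n)

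| r | Raw | Change | Adjusted |
|---|---|---|---|
| 0.3 | 0.258 | 0.306 | 0.246 |
| 0.5 | 0.258 | 0.258 | 0.224 |
| 0.7 | 0.258 | 0.200 | 0.184 |

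(r = 0.7 is shown only to extend the pattern.) Rewriting the CGI as a change score would not be the remedy: below r = 0.5 it is less precise than the raw score. Adjustment is at least as precise as either at every r shown.

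**Size of the gain.** Variance reduction is r², equivalent sample size is 30/(1 − r²), and power for 0.5 SD comes from the noncentral t with noncentrality 0.5/(0.258 × √(1 − r²)).

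| r | Variance reduction | Equivalent n per arm | Power |
|---|---|---|---|
| 0 (raw) | none | 30 | 47.8% |
| 0.3 | 9% | 33.0 | 51.4% |
| 0.5 | 25% | 40.0 | 59.4% |
| 0.6 | 36% | 46.9 | 66.3% |

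**Small-sample allowance.** Estimating the covariate slope inflates the adjusted variance by about 1 + 1/(60 − 4) = 1.018. The variance factors become 0.91 × 1.018 = 0.926 and 0.64 × 1.018 = 0.652, so the net reduction is about 7% to 35%. The power figures above do not include this allowance and are slightly generous.

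**The case against.** The strongest case against the point is that nothing here is an error. The raw comparison is unbiased, its type I error is correct, and the choice of covariates is often left to a statistical analysis plan, which may exist. If the CGI rates improvement, each score is already a judgement relative to the start, and a mean at each visit is a natural endpoint. The Discussion's interest in onset and maintenance is also served by the YGTSS change at weeks 4, 8 and 24. All of this stands, and it limits the point to precision on a secondary outcome. It does not remove the point: the article names a test, that test leaves collected information unused, and an improvement rating may also correlate with starting severity.

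Three stronger readings are tempting, and the documents do not support them.

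- **That no baseline CGI is scheduled.** The Outcome measures section lists endpoints and is not a visit schedule. The timeline is in Fig. 2, which is not shown, and no text says the CGI is omitted at baseline.
- **That adjustment would be impossible later.** The baseline YGTSS has to be collected and can serve as the covariate whatever the CGI version.
- **That chance imbalance between the arms adds error.** With 30 per arm the baseline means will differ by more than 0.3 SD in about 25% of trials; at r = 0.6 a difference of that size moves the raw CGI difference by 0.6 × 0.3 = 0.18 SD. That is ordinary sampling variation, already inside the standard error of 0.258.

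**Conclusion.** The point holds as a modest matter of efficiency. The stated analysis of the CGI discards baseline severity information that the trial necessarily holds, and adjusting for it would narrow the interval at each of the four visits.

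The size depends on a correlation that the documents do not give. Because YGTSS is a different scale from the CGI, its correlation with the later CGI is probably towards the lower end of the assumed range, where power moves only from about 48% to 51%. The upper figure of 66% needs r = 0.6, which is more plausible for a baseline rating on the CGI itself, if one exists. The power figures also rest on the assumed 0.5 SD effect and on 30 analysed per arm. The conclusions about the primary outcome and the sample size are untouched.

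**What to change.** In the Sample size and statistical analysis section, replace the t-test for the CGI with an ANCOVA at weeks 4, 8, 12 and 24: CGI score as outcome, arm as factor, baseline YGTSS total tic score as covariate. If a nonparametric approach is preferred for the CGI, a rank-based ANCOVA or a proportional-odds model can take the same covariate.

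In the Outcome measures section, say whether the CGI rates severity or improvement. If it rates severity and is rated at baseline, use the baseline CGI as the covariate instead.

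The cost is a sentence or two of text. With the YGTSS covariate, no new assessment or form field is needed, and every participant is covered, including those enrolled when the article was written ("To date, two participants have been recruited"). The covariate should be fixed before any outcome data are compared by arm.
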